**Figure 4 F4:**
[figure not shown]
Overview of the intervention mapping procedure.

To further tailor the intervention to the workers, the researchers performed a small qualitative evaluation of the work environment and occupational health services among the workers. The evaluation involved 1) observations of daily work life activities among the nurses’ aides as well as a short interview with the nurses’ aides and 2) observation of ergonomic classes held biannually in the municipality for the nurses’ aides. The data gathered in this phase indicated that activities should be carried out in proximity of their workplace and during their working time. The ergonomic classes focused on information of risk factors and training in manual patient handling and these factors were considered in the final content of the intervention activities, and documented in the intervention protocol. Finally, from the planning groups further adjustments will be made regarding the logistics of the activities, e.g. the one-hour physical training pr. week will be planned as once a week for one hour, twice a week for 30 minutes or whatever proves to be the most feasible for the individual team. The content of each of the activities will be described in further details in the following.

### Intervention

#### Participatory ergonomics

The overall aim of the participatory ergonomics in this study is to prevent physical exertion and pain through minimizing physical risk factors for LBP at work and reducing the work tasks perceived as physically demanding. Participatory ergonomics covers *"the involvement of the workers in planning and controlling significant amount of their own work activities, with sufficient knowledge and power to influence both processes and outcomes to achieve desirable goals"*[53]. The literature highlights participatory ergonomics as not being a unitary concept, but rather as an umbrella term covering a fairly broad range of ideas and practices
[54]. In this study, inspiration from the framework suggested by Haines et al.
[54] as well as the blueprint suggested by Wells et al.,
[55] was used in the development of the participatory ergonomics intervention. Therefore the participatory ergonomic process follows 6 steps: 1) identification of physically demanding work tasks, 2) analysis of physically demanding work tasks, 3) solution building, 4) prototype implementation, 5) evaluate prototype and 6) adopt solution. These steps will be carried out in two workshops of 3 hours and two follow-up meetings of one hour.

The participatory ergonomic process is initiated by a one-hour start-up meeting in each team. At this meeting, the ergonomic work group is formed. The ergonomic work group will consist of 5–7 employee team members and the instructor (a local therapist) will serve as the ergonomist. No supervisors are involved in the ergonomic work group. However they will be involved between workshops, as an employee (the ambassador) will present the decisions taken at the workshops for the supervisor. At the start-up meeting, all employees will have the opportunity to identify which work tasks they consider physically demanding and therefore a risk for development, maintenance and reoccurrence of pain. They are further encouraged to write down their suggestions and put it in an ergonomics mailbox situated at the workplace. The mailbox will be used throughout the intervention period and remain open for suggestions for the participatory ergonomic process from all the employees.

At the first workshop, the ergonomic work group will prioritize the identified physically demanding work tasks and analyze these. The results of this workshop should be 3–4 prioritized work tasks that should be 1) relevant (e.g. many workers perform the task or the task is done many times during a working day) and 2) be a significant risk factor for pain or it causes a high physical work exertion. At the second workshop, the ergonomic work group will come up with solutions to the prioritized work tasks and make an implementation plan. They are again asked to prioritize the solutions according to 1) efficiency (i.e. can this solution reduce pain or physical work exertion?) and 2) feasibility (i.e. is this solution likely to be implemented within the project period?). After the workshops, the solutions are to be implemented. At two follow-up meetings, the implementation of the solutions will be evaluated and possible adjustments made.

#### Physical training

The overall aim with the physical training in the study is to introduce different types of physical activities to the participants and motivate them to maintain the preferred physical training. The different types of physical training are chosen based on the evidence of efficiency as physical capacity building activities and their possible impact on preventing and reducing LBP. The physical training types are presented in 3 blocks: 1) body awareness and body postures, 2) strength and coordination training and 3) general physical activity. The physical training will be carried out each week for one hour with an instructor. It consists of twelve sessions with separate focus areas. The first four sessions will be introduction to physical training and the three different types of training. In the remaining sessions, the participants will be able to choose from the different types of training and develop their own training regime. During the sessions, different tasks will be incorporated that refers to ergonomic principles (e.g. manual handling of patients and good body postures) or cognitive behavioral principles (e.g. experience of acute vs. long term muscle discomfort/soreness/pain and training in relaxation techniques). Each training session starts with a warm up routine that will be the same for all twelve sessions and lasts approximately 15 minutes. The warm up routine consists of conditioning exercises involving large postural muscle groups as well as strengthening exercises for the abdomen and the lower back. The participants also receive a short brochure with description and illustrations of the exercises.

#### Cognitive behavioral training (CBT)

The CBT programme is a modified version of the program developed by Linton
[56] and further developed for a working population by Jørgensen et al.
[32]. The purpose of the programme is to reduce and prevent pain, and diminish negative effects of pain. All participants will be participating in two workshops of 3 hours. The workshops follow the same structure with a short lecture on the themes, problem-solving training and training of new skills (e.g. applied relaxation training). The first workshop will focus on improving the participants’ understanding of pain, the experience of pain, and the anticipation of pain by performing cognitive exercises on how physical activity may negatively or positively relate to pain. Another main focus will be on pain in relation to physical demanding work. The second workshop will focus on the ability to function and have a good life quality despite pain (i.e. pain coping, increasing health behavior, adapt skills to daily life). Moreover, the positive long-term effects from appropriate pain coping will be discussed
[56]. Finally, the participants will make their own individual plan for using the new skills and each team will make a plan on how to implement the new skills in their working day.

#### Maintenance

At the end of the intervention, the teams will prepare for the maintenance phase. In the maintenance phase, the ergonomic work groups will transform into an ergonomics and health promotion group. That means, that they will continue using the skills obtained during the participatory ergonomics programme (identification, analyses, solution building, prototype implementation, evaluate prototype and adopt solution), but will now broaden their scope to also include health-related challenges and solutions within health promotion methods. Still, the groups’ work will be based on input and suggestions from all employees and they will develop action plans on how to continue and maintain the activities after the 3 months of intervention.

#### Knowledge sharing

Throughout the three months period of intervention, the supervisors of the participating teams will attend three one-hour meetings, one each month. The main topics of these knowledge sharing meetings will be barriers and facilitators for implementation of the intervention. At these meetings, the researcher will be participating and guide the discussions. Minutes from the meetings will be distributed to the involving supervisors afterwards.

### Efforts for high compliance

An important focus in this study is to maintain high compliance throughout the study. It is well known that maintaining participants in the study and high participation is a difficult process in intervention studies at the workplace
[41]. Therefore, initiatives are taken to make participation more attractive and to minimize dropout. Firstly, the concepts of the project are participatory to ensure that the intervention is tailored to the specific needs of the participants facilitating ownership and motivation to participate in the study. We ensure that the entire organization is informed about the main features, purposes and processes of the project by having regular meetings. Written materials such as information letters, brochures and posters are distributed to the participants throughout the study period.

Furthermore, particularly for the stepped-wedge design, it is important that the same intervention content is delivered at each step (i.e. introduction of a new intervention group). To support this, the intervention mapping process was conducted to ensure the intervention was optimally tailored to the organization. Also, the intervention protocol was written with specific measureable criteria for delivery of the intervention. Finally, pre-developed expectation materials are delivered to all stakeholders of the intervention. Moreover information to support organizational level decisions about dissemination of the intervention content to other departments is withheld as long as possible until proper systematic evaluation can be conducted when all four intervention deliveries are finalized.

### Data collection

The data collection consists of text messages and questionnaires. At baseline the participants also received physiological health measures for describing the health of the population.

### Physiological health measures

To map the health of the employees and to motivate them to participate in the intervention, all participants were invited to physiological health measures at baseline. The height was measured with no shoes and in upright standing position (Seca 230). Body weight, body mass index (BMI) and body fat percentage was determined using bio impedance (TANITA BC-418). Resting blood pressure was measured on the left arm after at least 15 minutes sitting rest (Omron M3)
[57]. Participants received individual feedback on the results from the health measures in regard to Danish and international guidelines
[57,58]. All measurements were performed by trained clinical personnel (physiologists and physiotherapists).

### Evaluation

Analyzing the effects and processes of a complex intervention requires a comprehensive evaluation. In order to match the design and context of this project, the efficiency of the study will be evaluated. The study efficiency will be a result of both efficacy and implementation (Efficiency = Efficacy X Implementation)
[59].

### Primary outcome measures

Because LBP is a fluctuating condition, which can be difficult to recall
[60], monthly monitoring will be conducted by using mobile phone text messages. In addition to the frequent measuring of LBP, consequences (i.e. bothersomeness due to LBP) will also be measured monthly by text messages delivered by the SMS Track® system
[61,62]. The setup of the software is designed for the study in close cooperation with researchers. Every month (on a Monday) the respondents receive an automated text message to their private mobile phone, which they are expected to answer by using a text message. LBP is measured as days with pain and intensity of pain in the lower back each month throughout the data collection period. The questions posed are "*During the previous four weeks, how many days have you had low back pain?"* and *"What was the highest intensity of your low back pain, with 0 being no pain and 10 being the worst imaginable pain?"* Consequences of pain will be measured by days with bothersomeness due to LBP each month throughout the data collection period. In a recent consensus report to standardize LBP measures, the description "limit your usual activities or change your daily activities" was suggested to measure the severity of pain
[63]. Moreover, bothersomeness has shown to correlate well with quality of life
[64], thus making a good measure for consequences of LBP. The question posed is *"How many days during the previous four weeks has your low back pain been bothersome (*i.e. *affected your daily activities or routines)?"*

### Secondary outcome measures

Self-reported sickness absence due to LBP is obtained monthly by text message
[65]. Additionally, every three months the following will be measured by text messages: Work ability
[66], Occupational lifting and carrying
[67], Self-rated physical exertion
[68], Self-rated muscle strength
[69], fear avoidance beliefs
[70] as well as support from management regarding support to handle musculoskeletal pain.

### Process evaluation (implementation)

An evaluation of the implementation will be performed, inspired by the framework by Steckler and Linnan
[71] to gain insight into the extent to which the intervention is implemented as intended
[59]. The implementation will be measured through dose delivered (the amount of intervention components actually delivered by the instructors) and dose received (employees participation in the activities)
[71]. The delivery will be measured by asking the instructors to what extend they have followed the specific intervention activities in accordance to the defined criteria written in the intervention protocol (they will fill out a questionnaire after each activity). The dose will be measured by participation rate and by questionnaires to the participants after the intervention asking about their appraisal of the intervention
[71].

### Sample size calculation

For sample size calculation we used the method described by Woertman et al.
[72] for the stepped wedge design. The sample size is calculated for LBP intensity (numeric rating scale 0–10). Due to the fact that we were not able to find any relevant studies on workplace interventions measuring LBP intensity, we estimated variance from the study by Kovacs et al. on patients with non-specific low back pain
[73]. The variance was set to 2.1. With an α of 0.05, a power of 0.8, and an intracluster correlation coefficient of 0.05, we calculated that we needed 65 participants in a stepped-wedge trial to allow analyses of LBP intensity.

The sample size calculation was based on a patient group meaning that all subjects will have pain and thereby it is possible to reduce pain in all subjects. The present study is a workplace intervention where all employees are invited to participate. Therefore we expect to enroll both participants with and without pain, meaning that we need a bigger sample size in order to detect a difference in LBP intensity. Workplace studies often have a high drop-out rate and could be expected to be up to 50%. When conducting a stepped wedge design, the intervention period is prolonged. This can be an extra risk factor for a high drop-out rate due to a high turn-over rate or due to "fatigue" relating to waiting for receiving the intervention. Moreover there is a greater risk for organizational changes happening at the workplace during the study period, meaning that we could lose entire clusters in the evaluation. Giving that we have a workplace willing to offer the intervention to all employees, we chose to randomize all 594 who wanted to participate and therefore should have sufficient power to detect an effect on LBP intensity even when taking all of the above concerns into consideration.

### Statistical analysis

Baseline characteristics will be described by questionnaires and the physiological health measures. Analyses regarding the effectiveness of the primary outcomes and secondary outcomes will be performed after three months of intervention by means of multilevel analyses suggested by Hussey & Hughes (linear mixed model (LMM) or generalized linear mixed models (GLMM))
[74]. Multilevel analyses take clustering of observations of workers within the same team into account, as well as repeated measurements within one participant
[75]. The analyses will be conducted for the different measures of LBP; intensity, days and bothersomeness. Moreover, we will investigate whether the combined measure of the three measures of LBP will fulfill the criteria for a LBP index and investigate the effect on the LBP index.

All statistical analyses will be performed according to an intention-to-treat principle. In addition, per protocol analyses will be conducted for those groups that actually complete the intervention protocol. Further, in a subgroup analysis the effect on only the population of nurses’ aides will be evaluated.

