## Methods

### Study design

The study is described in accordance to the guidelines of the Consort Statement
[50]. In clinical intervention research, the randomized controlled trial (RCT) is considered the gold standard. However, in workplace settings the introduction of control groups not receiving intervention can hamper implementation due to logistical issues and impaired organizational commitment
[48,49]. Moreover, it is impossible to implement the intervention in many clusters simultaneously because of practical and logistical reasons. These difficulties can be overcome in the more feasible stepped wedge design
[48,49] with gradual implementation of the intervention in different teams. Therefore, this study uses a stepped-wedge cluster-randomized controlled trial design with 4 groups (594 participants in total) (Figure 
2). A stepped-wedge design is a type of crossover study in which clusters cross over from the control arm to the intervention arm at different time points
[48,49]. Twenty-one clusters were formed based on working teams, and randomly assigned to four successive time periods three months apart and enrolled in the study in accordance with the stepped-wedge group order. The project began in November 2012 with baseline measurements and was followed by a 3 months burn-in period without intervention activities but with repetitive baseline measures. The intervention began in February 2013.

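### If the Hussey & Hughes model is fitted with team and participant effects only, as the article describes it, any team-specific change over time would make its intervals too narrow

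*Protocol article*

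**What the plan says.** The Statistical analysis section of the Protocol article says the primary and secondary outcomes will be analysed "by means of multilevel analyses suggested by Hussey & Hughes", as a linear or generalised linear mixed model. It explains the choice with "Multilevel analyses take clustering of observations of workers within the same team into account, as well as repeated measurements within one participant". No team-by-period term, decaying team correlation, robust variance or small-sample correction is mentioned, and the random effects are not written out.

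The Sample size calculation section plans with a single intracluster correlation: "With an α of 0.05, a power of 0.8, and an intracluster correlation coefficient of 0.05, we calculated that we needed 65 participants". It also states "The variance was set to 2.1". The Study design section gives "Twenty-one clusters were formed based on working teams", 594 participants, a three-month burn-in and four steps three months apart. The Primary outcome measures section gives monthly measurement by text message.

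**The concern.** The standard Hussey & Hughes model has one constant random effect per cluster and a time course shared by all clusters. Adding a participant effect handles repeated measures. It still treats two colleagues as equally correlated whether they are measured in the same month or a year apart.

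A stepped wedge draws its effect estimate largely from change within clusters over time. Constant team and person effects mostly cancel out of that comparison; a change specific to one team in one period does not. A shared month effect cannot absorb it, and a model without a term for it counts it as independent noise averaged over some 28 people. At stake are the confidence intervals and p-values for low back pain intensity, days and bothersomeness.

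**Working it through.** **The plan's own figure.** The 65 participants cannot be reproduced from the stated inputs, because no target difference is given. The point here does not depend on it. What is taken from that section is the intracluster correlation of 0.05 and the variance of 2.1.

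**Inputs from the article.** 21 teams, split here 6/5/5/5 over the four steps; 594/21 = 28.3, so 28 per team; 3 + 4 × 3 = 15 monthly measures (the 15 months are derived, not stated); intracluster correlation (ICC) 0.05; drop-out of up to 50%, which would leave 14 per team.

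**Assumed inputs, not in the article.**
- Cluster autocorrelation (CAC), the share of the team variance that stays constant from quarter to quarter: 1.0 to 0.80.
- Person share, the part of the remaining variance that is constant within a participant: 0.3 to 0.7.
- Equal team sizes, a continuous outcome, no missing data, and the same intervention effect in every team.

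**Method.** The working model has fixed month effects and constant random team and person effects. Its variance components are set to the values it would converge to under the true covariance. Its model-based SE is then compared with the true (sandwich) SE when part of the team variance changes by quarter. With R = true SE / model SE, the true type I error is 2 × [1 − Φ(1.96/R)].

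**Hand check (total variance 1, ICC 0.05, person share 0.5).** The monthly residual variance is 0.95 × 0.5 = 0.475. The noise in a team's quarterly mean is 0.475/(28 × 3) = 0.00565. The team-by-quarter variance is 0.05 × (1 − CAC).
- CAC 0.95: 0.0025, R ≈ √(1 + 0.0025/0.00565) = 1.20
- CAC 0.90: 0.0050, R ≈ √(1 + 0.0050/0.00565) = 1.37
- CAC 0.80: 0.0100, R ≈ √(1 + 0.0100/0.00565) = 1.66

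The full calculation gives R = 1.20, 1.36 and 1.64. For CAC 0.90, 1.96/1.36 = 1.44, so the type I error is 0.15.

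**True type I error of a nominal two-sided 5% test, full calculation:**

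| ICC, people per team | CAC | share 0.3 | share 0.5 | share 0.7 |
|---|---|---|---|---|
| 0.05, 28 | 1.0 | 0.05 | 0.05 | 0.05 |
| 0.05, 28 | 0.95 | 0.09 | 0.10 | 0.14 |
| 0.05, 28 | 0.90 | 0.12 | 0.15 | 0.21 |
| 0.05, 28 | 0.80 | 0.19 | 0.23 | 0.32 |
| 0.05, 14 | 0.95 | 0.07 | 0.08 | 0.09 |
| 0.05, 14 | 0.90 | 0.09 | 0.10 | 0.13 |
| 0.05, 14 | 0.80 | 0.12 | 0.15 | 0.20 |
| 0.01, 28 | 0.95 | 0.06 | 0.06 | 0.07 |
| 0.01, 28 | 0.90 | 0.06 | 0.07 | 0.08 |
| 0.01, 28 | 0.80 | 0.08 | 0.09 | 0.12 |

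**Simulation check** (2,000 data sets per setting, variance components estimated, ICC 0.05, share 0.5, 28 per team): 0.046, 0.101, 0.144 and 0.232 at CAC 1.0, 0.95, 0.90 and 0.80. Changing only the reference distribution to t with 19 degrees of freedom leaves 0.20 at CAC 0.80. Analysis with the team-by-quarter term and known components gave 0.04-0.06.

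**Sensitivity.** Cutting each team's data at three months after crossover, the follow-up named in the abstract, changes almost nothing (0.23 at CAC 0.80, share 0.5). A team correlation that decays over quarters is somewhat worse (about 0.29 at 0.80).

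**Standard errors on the outcome scale** (variance 2.1, so multiply by √2.1 = 1.449; share 0.5). Model-based: 0.0267 × 1.449 = 0.039. True: 0.0364 × 1.449 = 0.053 at CAC 0.90 and 0.0440 × 1.449 = 0.064 at CAC 0.80.

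**The case against.** The strongest reply is that the model under criticism is partly inferred. The article names a method and gives a general reason for multilevel analysis. It does not list the random effects or say that they are constant or the only ones, and a covariance structure may be settled in an analysis plan that is not shown. That stands as a limit on the wording: a reader might infer that the plan fixes constant effects only, and the text does not go that far. It does not remove the point. The article names a specific model whose standard form has no team-by-period term, and names only two correlation sources. A better specification can be recommended against that description.

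A reader might also take "Moreover there is a greater risk for organizational changes happening at the workplace during the study period" as the plan's own forecast of team-specific drift. It is not. The sentence goes on to the risk of losing whole clusters and serves to justify the sample size. A random team-by-period effect does not deal with a lost cluster. The article therefore gives no direct evidence that drift will occur, and the inflation is nil if the autocorrelation is 1.0.

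Nor do the figures support saying that unmodelled drift dominates the error throughout. At ICC 0.05, 28 per team and share 0.5, its part of the true error variance is 1 − 1/R²: 30% at CAC 0.95, 46% at 0.90 and 63% at 0.80. It passes half only in the last case.

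Finally, the calculation covers a linear mixed model. It was not run for a generalised model or for the censored analysis planned for hypothesis 2, and missing data and effects that vary between teams were not tested.

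**Conclusion.** The point holds in conditional form. If the analysis is fitted as described, with team and participant correlation only, team-specific change over time would make the standard error too small. At the plan's ICC of 0.05 and about 28 per team, an autocorrelation of 0.95 between quarters would already put a nominal 5% test at 9-14%; at 0.80 it would be 19-32%. The problem shrinks to about 7-20% over the same autocorrelations with 14 per team, and to about 6-12% at ICC 0.01. All these ranges rest on an autocorrelation and a person share that the article does not supply.

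The error rates do not depend on the outcome variance. The outcome-scale standard errors do: they use 2.1 as a variance, as the article calls it, and would be larger by a factor of 1.449 if it were a standard deviation. The change is worth making before analysis. Confidence is medium, because the size cannot be fixed from the document.

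**What to change.** State the primary linear mixed model as: month as a fixed effect; random intercepts for team and participant; and a random team-by-quarter effect, or a team correlation that decays over time. Add a small-sample correction for 21 clusters, such as Kenward-Roger for the linear mixed model. The correction alone is not enough, as the t-reference result shows. State the corresponding structure for any outcome analysed with a generalised model.

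If a permutation test is added as a check, it must re-randomise by the scheme actually used. The Randomization section describes district strata and allocation in order of cluster size, so shuffling clusters freely within district would not reproduce it.

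The cost is analysis wording, with no change to design or data collection. If drift exists, intervals widen (SE about 0.053-0.064 against 0.039 at CAC 0.90-0.80, variance 2.1, share 0.5), and power falls accordingly. If it does not, the added variance should be estimated near zero and little is lost.

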## Discussion

This paper presents the design of a stepped-wedge cluster randomized controlled trial to investigate the effectiveness of a multi-faceted workplace intervention among nurses’ aides combining participatory ergonomics, physical training and CBT. To our knowledge, this is one of the most comprehensive intervention studies among nurses’ aides conducted at the workplace. Intervention effectiveness trials for preventing and reducing LBP and its consequences in workplaces with physically demanding work are few, and mostly unsuccessful. Part of the reason for negative results may be that most previous interventions have been carried out as single-faceted interventions that only address one aspect of the multi-factorial origin of LBP. Establishing the effectiveness of a multi-faceted intervention in workplace settings among high-risk groups such as nurses’ aides is therefore necessary.

Strict adherence to a traditional RCT design may hamper implementation and compliance. Therefore, by using a stepped-wedge design as a means to improve implementation and establishing the effectiveness of a multi-faceted intervention will provide knowledge of prevention of LBP and its consequences in workplace settings among high-risk groups such as nurses’ aides. Moreover having a participatory concept throughout the study and involving the organization and focus on supervisors, as important drivers of change will potentially promote implementation of the intervention.

Only a few studies have focused on the natural course (i.e. development without interventions) of LBP in detail
[2] and no studies have focused on the course of LBP in detail after an intervention. An accurate description of a fluctuating condition such as LBP may require several points of measurement over time to describe the course in detail. Measuring pain can possess a risk of recall-bias
[60,76]. By using frequent measures of LBP the study will contribute to a more detailed description of the natural course of LBP among workers and a possible reduction of LBP during the intervention. Many previous studies have not been able to show a significant reduction in pain among workers

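### The named multilevel model, in its ordinary form, would understate the standard error of the intervention effect if a worker's monthly pain replies are serially correlated; the within-worker correlation should be specified as decaying over time, or a cluster-robust variance used

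*Protocol article*

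**What the plan says.** The protocol article, Statistical analysis, plans "multilevel analyses suggested by Hussey & Hughes", as an LMM or a GLMM, for the primary and secondary outcomes. It adds that such analyses allow for clustering by team "as well as repeated measurements within one participant". The analyses are to be run for pain intensity, days with pain and days with bothersomeness. The section names no residual structure over time, no serial term and no robust variance.

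The outcome is described under Primary outcome measures: "Because LBP is a fluctuating condition, which can be difficult to recall", it is asked about by text message every month, each question on days covering the preceding four weeks. The Discussion repeats the idea: "An accurate description of a fluctuating condition such as LBP may require several points of measurement over time".

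Study design gives 594 participants, 21 clusters, four steps three months apart and a three-month burn-in with repeated baseline measures. The missing-data section fills gaps by last observation carried forward (LOCF) for hypotheses 1 and 3, and censors at the first missing measurement for hypothesis 2.

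**The concern.** The article names a model and states that its levels deal with the repeated measurements. A worker intercept deals only with a constant difference between workers. It does not deal with a pain episode that runs over two or three neighbouring months. In a stepped wedge the intervention indicator is itself an unbroken run of months, so such an episode is easily mistaken for an intervention effect, or for the lack of one. A standard error based on independent residuals leaves this out.

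This variance component differs from change shared by a whole team. It arises even when no team-level change exists, so a team-by-month effect does not pick it up. At stake are confidence intervals that are too narrow and an inflated chance of declaring an ineffective programme effective.

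**Working it through.** The documents give no type I error or autocorrelation to reproduce. The stated sample size has no bearing on this point.

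**Inputs from the article.** 594 / 21 ≈ 28 workers per cluster. Months: 3 burn-in + 4 × 3 = 15. From Sample size calculation: "With an α of 0.05, a power of 0.8, and an intracluster correlation coefficient of 0.05" (two-sided testing assumed). For the variance: "The variance was set to 2.1"; it cancels from the type I error, so total variance is scaled to 1.

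**Assumed, because the article does not give it.** Team variance 0.05 (matching the ICC: 0.05 / 1.00), worker variance 0.45, residual variance 0.50. Residual covariance between months s and t is 0.50 × ρ^|s−t|, with ρ = 0, 0.3, 0.5, 0.7. Clusters per step 6, 5, 5, 5. No missing data.

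**Method.** The fitted covariance V has team and worker intercepts and independent residuals, with its variance components set to best-fitting values. The true covariance is Σ. X holds the month effects and the intervention indicator.
- Model variance: (X′V⁻¹X)⁻¹
- True variance: (X′V⁻¹X)⁻¹ X′V⁻¹ΣV⁻¹X (X′V⁻¹X)⁻¹
- Type I error: 2[1 − Φ(1.96 × SE_model / SE_true)]

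**Results, all 15 months.**

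| ρ | SE model | SE true | Ratio | Type I error |
|---|---|---|---|---|
| 0 | 0.0273 | 0.0273 | 1.00 | 5.0% |
| 0.3 | 0.0265 | 0.0323 | 1.22 | 10.8% |
| 0.5 | 0.0256 | 0.0350 | 1.37 | 15.3% |
| 0.7 | 0.0235 | 0.0352 | 1.50 | 19.1% |

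For ρ = 0.5: 1.96 / 1.371 = 1.43, and 2[1 − Φ(1.43)] = 0.153.

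**Sensitivity.**
- Months cut at three after crossover (the groups then contribute 6, 9, 12 and 15 months): about 10.5%, 15% and 19% for the same ρ. With ρ = 0.9 it reaches about 23%.
- If 0.3 of the 0.5 residual variance is independent reply noise: 7.2%, 8.9% and 9.9%.
- ρ = 0.1 with no reply noise: 6.7%.

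**Simulation of null trials, all months.**

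| Fitted model | ρ 0.3 | ρ 0.5 | ρ 0.7 |
|---|---|---|---|
| Team and worker intercepts | 11.3% | 15.9% | 18.7% |
| plus team-by-month effect | 10.8% | 15.0% | 17.5% |
| plus worker-level AR(1) | 5.1% | 4.6% | 4.0% |

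These are 2,000 runs per setting. A separate set of 500 runs gave, at ρ = 0.3 and 0.7, 9.0% and 17.2% for the first model, 7.8% and 16.2% with the team-by-month effect (its variance typically estimated at about zero), and 4.2% and 4.4% with AR(1). Replacing the z test by t on 19 degrees of freedom gave 6.8% and 15.0% for the first model.

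**LOCF.** With ρ = 0 but 20% of replies missing at isolated months (assumed rate) and filled by LOCF, 1,500 runs gave type I error of 9.7% (SE ratio 1.15). LOCF after permanent drop-out alone did little: SE ratio about 1.05 at 50% drop-out.

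**Interval width under the fix.** The standard error under the correct decaying-correlation model, divided by the ordinary model's SE, is 1.17, 1.19 and 1.10 (all months) and 1.17, 1.23 and 1.20 (three-month window) at ρ = 0.3, 0.5 and 0.7. With reply noise, also included in the model, it is 1.08 to 1.14.

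**The case against.** A reader might infer that the plan declares all of a worker's replies equally correlated. It does not: no random intercept, independent residual or exchangeability is written down, and an LMM with an autoregressive residual would satisfy the sentence. The residual structure is also something that an analysis plan, not shown here, may fix. This stands, and the point is therefore about the ordinary form of the named model. It does not dispose of the point, because the article claims that the model's levels account for the repeated measurements, and in that ordinary form they do so only if correlation does not decay.

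Second, calling the condition fluctuating does not establish carry-over from month to month, and no autocorrelation is given. This also stands: the size is conditional and falls to 5% with no decay. But carry-over is plausible for consecutive four-week windows, and LOCF makes adjacent months alike by construction wherever replies are missing.

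Third, a reader might extend the point to every primary analysis. The censoring rule for hypothesis 2 suggests an event-type analysis, to which this residual structure would not apply.

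Fourth, the AR(1) remedy was not tested together with LOCF, so its return to about 5% is shown for complete data only. That limit stands.

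**Conclusion.** The point holds as a conditional risk. If the named model is fitted in its ordinary form and replies are serially correlated, the standard error of the intervention effect is too small: by 18% to 33% (1 − 1/1.22 to 1 − 1/1.50) at ρ = 0.3 to 0.7 with no reply noise, giving type I error of about 11–19%. With substantial independent reply noise it is about 7–10%, and with no decay 5%. A fixed error of 11–19% cannot be read off the documents, since the autocorrelation and the worker–residual variance split are assumed. The point covers intensity, days and bothersomeness as repeated measures under hypotheses 1 and 3. A correction limited to team-by-month change would leave it in place. It should be settled before analysis, since the choice of structure affects the width of the intervals.

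**What to change.** In Statistical analysis, add a sentence stating that the LMM includes, beyond the cluster and worker effects, a within-worker correlation that decays with months apart (AR(1) or exponential), and that a GLMM includes an autoregressive worker-level effect. Alternatively, for either model, state that the variance is estimated robustly at the level of the 21 randomised clusters with a small-sample correction; this does not depend on having the shape of the decay right.

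The cost is one sentence and slightly more computing. Under the decaying-correlation model, intervals would be about 8–23% wider in the scenarios above. If there is no decay, almost nothing is lost.
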